### Interim analyses {21b}

An interim analysis will be performed on the primary endpoint when 20% of participants have completed the eight weeks of PEMF. The interim analysis ensures that there is no serious adverse event that happened during the study period.

### Methods for additional analyses (e.g. subgroup analyses) {20b}

The heterogeneity in tendinopathy will be addressed by sub-group analysis. AT will be categorised into midportion and insertional tendinopathy. The assessor will make the diagnosis of the type of Achilles tendinopathy. Midportion AT will be diagnosed by local thickening and a colour doppler flow of at least two out of four in the modified Öhberg score 2–6 cm proximal to the insertion of the Achilles tendon. Insertional AT will be diagnosed by local thickening and colour Doppler flow of at least grade two of four in the modified Öhberg score within 2 cm of the insertion of the Achilles tendon. Sub-group analysis will be performed to understand if PEMF has clinical effects on all outcome measures in the midportion tendinopathy and insertional tendinopathy, respectively, since the number of participants will be smaller in the subgroups. A non-parametric test, the Mann–Whitney *U* test, will be used to detect if there are significant differences in the outcomes for each subgroup.

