**Inclusion criteria**
(1) Age between 18 and 70 (2) Focal clinical signs of AT with localised tenderness on palpation of the Achilles tendon (3) Recurrent complaints in 1 or both Achilles’ tendons at rest and during exercise for the preceding 3 months (4) Structural changes of the tendon were confirmed via sonographic examination during the initial physical exam (5) Informed consent

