## Statistical methods

### Statistical methods for primary and secondary outcomes {20a}

Statistical analysis will be performed using SPSS software (SPSS 26.0) based on the intention-to-treat principle. The normality of the data will be tested using the Kolmogorov–Smirnov test. A repeated-measures two-way analysis of variance (ANOVA) will be used to compare muscle strength, ankle range of motion, and results of questionnaires at baseline, 4 weeks, 8 weeks, and 3-, and 6-month follow-up. A nonparametric Mann–Whitney *U* test will be used to compare questionnaire results (ordinal data) between control and experimental groups. Subgroup analysis for participants with mid-portion or insertional AT will also be performed using interaction tests from ANOVA. Significant differences for each test measuring physical function will be based on an alpha level set at 0.05.

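### The midportion/insertional subgroup analysis is given two different tests with no rule on which governs, and its two categories need not hold every eligible patient exactly once

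*Protocol article*

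**What the plan says.** The protocol article describes this subgroup analysis twice.

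- **Statistical methods for primary and secondary outcomes {20a}:** "Subgroup analysis for participants with mid-portion or insertional AT will also be performed using interaction tests from ANOVA".
- **Methods for additional analyses {20b}:** the aim is to learn whether PEMF has clinical effects on all outcome measures in each of the two types. The test is a Mann–Whitney U test that "will be used to detect if there are significant differences in the outcomes for each subgroup". The reason apparently given for the non-parametric test is "since the number of participants will be smaller in the subgroups".

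Section {20b} also defines the subgroups. It says "AT will be categorised into midportion and insertional tendinopathy". Midportion disease needs "local thickening and a colour doppler flow of at least two out of four in the modified Öhberg score 2–6 cm proximal" to the insertion. Insertional disease needs "local thickening and colour Doppler flow of at least grade two of four in the modified Öhberg score within 2 cm of the insertion".

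The imaging criterion for entry (Table 1, inclusion criterion 4) is wider: "Structural changes of the tendon were confirmed via sonographic examination during the initial physical exam". It sets no Doppler grade, no thickening and no location. Criterion 3 admits disease in one or both tendons. The modified Öhberg scale in the Neovascularity part of Outcomes {12} runs from 0 to 4+, so grades 0 and 1+ lie below the subgroup threshold.

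**The concern.** The two tests answer different questions. An arm-by-site interaction asks whether the PEMF effect differs between midportion and insertional disease. A test inside each subgroup asks whether an effect can be detected there. One significant and one non-significant subgroup result is not evidence that the effects differ, and small subgroups produce that pattern readily by chance. With both methods in the plan and no ranking, the report could rest a site-specific claim on whichever gives the more interesting answer.

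The second problem is membership. The text sets out to sort AT into two types, but the rules for the types are stricter than the rules for entry. Eligible patients below the Doppler threshold, or without thickening, have no place. Patients affected at both sites, in one tendon or in two, have two places and no rule for choosing. The subgroup results could then describe an undeclared subset of the randomised patients.

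**Working it through.** **Consistency of the text.** Sections {20a} and {20b} name the same two subgroups, give different tests, and do not refer to each other. The membership rules compare as follows.

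| Requirement | Entry (Table 1) | Midportion {20b} | Insertional {20b} |
|---|---|---|---|
| Structural change on ultrasound | yes, unspecified | as thickening | as thickening |
| Öhberg grade ≥ 2 | no | yes | yes |
| Location | none set | 2–6 cm | within 2 cm |

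A patient with grade 0 or 1+, or with structural change but no thickening, can meet entry and neither definition. A patient meeting the criteria in both zones meets both. No third category is given.

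**Size of the first problem.** The plan attaches no figure to the subgroup analysis, so there is none to reproduce. Inputs from Sample size {14}: difference 16, pooled SD 20.25, 40 participants, 20% dropout; standardised difference 16/20.25 = 0.79. Assumptions: a single time point, normally distributed scores, two-sided 5%, equal arms within each subgroup, and the site split, which the document does not give.

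Simulated Mann–Whitney power with the full 16-point effect:

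- 10 v 10: 0.345
- 14 v 14: 0.49
- 6 v 6: 0.21
- 8 v 8 (a 20/20 split after 20% dropout): 0.30

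The subgroups are independent, so with powers p and q, P(exactly one significant) = p(1 − q) + q(1 − p).

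- 20/20 split: 2 × 0.345 × 0.655 = 0.45. Neither: 0.655² = 0.43. Both: 0.345² = 0.12.
- 28/12 split: 0.49 × 0.79 + 0.21 × 0.51 = 0.49.
- 20/20 with 20% dropout: 2 × 0.30 × 0.70 = 0.42, using exact p-values (about 0.38 with the normal approximation to the rank test).
- No effect at either site, nominal 5%: 2 × 0.05 × 0.95 = 0.095, slightly less where the discrete rank test runs below its nominal level.

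**Power of the interaction test.** For subgroup totals a and b, SE = 20.25 × √(4/a + 4/b). Power to detect a 16-point difference in effect between sites is Φ(16/SE − 1.96) plus a negligible opposite tail. The detectable difference at 80% power is 2.80 × SE.

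- 20/20: SE = 20.25 × √0.40 = 12.81; 16/12.81 = 1.25; power 24%; detectable difference about 36 points.
- 30/10: SE = 20.25 × √0.533 = 14.79; 16/14.79 = 1.08; power 19%; detectable difference about 41 points.
- With 20% dropout these powers fall to about 20% and 16%.

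**The case against.** The strongest reply is that the sections do not strictly collide. Section {20a} says the interaction tests will *also* be performed, and {20b} asks whether PEMF works in each type, which a two-sample test within each type does address. Nothing in {20b} says that a site difference will be inferred by comparing two p-values. This stands in part: both analyses may be intended. But the document does not say so, and it does not say which one decides whether the effect differs by site.

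Four stronger readings are tempting and are not supported.

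- *The trial will usually report an effect at one site only.* At 20/20, the subgroups agree more often than not (43% neither plus 12% both = 55%). Discordance nears one half only with the full effect at both sites and an uneven split, and is about 9–10% with no effect.
- *Some enrolled patients certainly fit neither subgroup.* The criteria make this possible. The entry term for structural change is not defined in the article, and no figure is given for how many patients would be affected.
- *The trial's result rests on a subset selected by vascularity.* The main comparison is by intention to treat ({20a}, {20c}); only the subgroup analysis could lose patients.
- *Using Doppler grade is a fault because it is also an outcome.* Subgrouping on the baseline value of an outcome is ordinary practice, and nothing indicates that post-treatment grades would be used.

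**Conclusion.** The point holds as one to reconcile in a secondary analysis. The mismatch between {20a} and {20b}, and the gap between the subgroup definitions and the entry criteria, follow directly from the text.

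The consequence is conditional. With an identical 16-point effect at both sites, relying on the within-subgroup tests would show one significant site in about 42–49% of trials. This assumes a 20/20 to 28/12 split, or 20/20 with 20% dropout, at a single time point. A reader of such a result could wrongly conclude that PEMF works at one site only. The number of patients who would be unclassified or doubly classified cannot be determined from the document.

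**What to change.** 1. State in both sections that the arm-by-site interaction on VISA-A is the only test of whether the PEMF effect differs by site.
2. In {20b}, replace the within-subgroup Mann–Whitney p-values with site-specific differences between arms and 95% confidence intervals, labelled exploratory.
3. Assign every randomised participant to one category from baseline findings. Either classify by location without the Doppler threshold, or keep the present definitions and add a category for unclassified or both sites. The second option leaves the trial's own diagnostic definitions intact.

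**Cost.** This is mostly wording. The interaction test gains no power: 19–24% for a 16-point difference in effect before dropout, so it guards against a false site-specific claim but is unlikely to establish a true one. Section {20a} lists both ANOVA and Mann–Whitney for questionnaire results, so the model carrying the VISA-A interaction must be named. The document describes a diagnosis of type that includes a Doppler threshold, not a separate record of location. Enrolment began in July 2021 (Trial status), so baseline records of participants already enrolled may need to be checked for location.

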### Methods in analysis to handle protocol non-adherence and any statistical methods to handle missing data {20c}

The intention-to-treat analysis will be used to include all study participants in the groups to which they are randomised, regardless of any departures from the original assigned group. The missing values will be estimated by multiple imputations with the assumption that values are missing at random.

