### Outcomes {12}

#### Patient-reported outcomes

The primary outcome is the score of the Victorian Institute of Sports Assessment-Achilles (VISA-A) questionnaire, which is explicitly designed for Achilles tendinopathy. VISA-A will be used to evaluate pain and symptom severity with activity in participants with AT. Chinese-speaking participants will complete the validated VISA-A HK questionnaire [8]. The VISA-A questionnaire covers three domains associated with AT: pain, function, and sporting activities. A deterioration in self-reported pain, function, and sporting activities is the critical reason patients with AT come for medical consultation. Improving questions covered in VISA-A is often the rehabilitation goal for these patients. Since PEMF was used for pain reduction for other musculoskeletal disorders, similar effects may be applied to patients with AT.

Short Form-36 questionnaires (SF-36) will be used to evaluate health-related quality of life [9]. PEMF may reduce pain levels and allow participants to resume social activities, recreational activities, and functional tasks at work. A numeric pain rating scale (NPRS) will be used to assess the level of pain on the categories “general on the day of review,” “family and responsibility at home,” “recreation,” “social activities,” and “running training or other physical activities.” Each NPRS ranges from “no pain” to “severe pain”.

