### Sample size {14}

A minimum clinically significant difference is 16 points on the VISA-A scores based on the pilot study using VISA-A as the primary outcome in treating AT [18]. It was reported in a feasibility study using another conservative treatment, laser therapy as an adjunct treatment to eccentric exercise therapy for AT. A total of 20 participants were recruited and VISA-A was the primary outcome. Significant improvements were shown in both treatment groups in VISA-A [18]. The power calculation to detect the minimum clinically significant difference is conducted using the G Power programme at a type I error of 5%, power of 80% (correlation value, 0.03; pooled SD, 20.25). Twenty subjects per group are obtained to detect a significant difference in VISA-A among two groups if a two-way repeated-measures analysis of variance (ANOVA) is proposed. It is expected to have a 20% dropout rate. Thus, the final study sample size is 40 subjects in total [19].

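### Multiple imputation of VISA-A is paired with an ANOVA F test and a Mann–Whitney U test, neither of which is set up to give a poolable between-arm difference to compare with 16 points

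*Protocol article*

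**What the plan says.** All references are to the protocol article.

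- Outcomes {12}: "The primary outcome is the score of the Victorian Institute of Sports Assessment-Achilles (VISA-A) questionnaire".
- Statistical methods for primary and secondary outcomes {20a}: "A repeated-measures two-way analysis of variance (ANOVA) will be used to compare muscle strength, ankle range of motion, and results of questionnaires at baseline" and at the four follow-ups. In addition, a Mann–Whitney U "test will be used to compare questionnaire results (ordinal data) between control and experimental groups". VISA-A is a questionnaire, so both methods apply to it.
- Methods to handle non-adherence and missing data {20c}: "The intention-to-treat analysis will be used to include all study participants in the groups to which they are randomised", and "The missing values will be estimated by multiple imputations with the assumption that values are missing at random".
- Sample size {14}: a 16-point minimum clinically significant difference, pooled SD 20.25, 20 per group, and "It is expected to have a 20% dropout rate".

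Sections {20a} and {20c} do not name a between-arm VISA-A estimate, a primary visit, or which of the two tests decides.

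**The concern.** Rubin's rules combine an effect estimate and its standard error across imputed data sets. The plan names two hypothesis tests, whose direct output is an F or a U with a p-value for each imputed data set. Someone who follows the text literally holds one p-value per imputed set and per test, and must still find a way to one answer. The simple ways (analyse one imputed set, or average the imputations and test once) treat imputed values as if they had been observed, and so overstate certainty.

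The second issue is what the tests answer. The trial was sized on a difference in VISA-A points, and neither test as named reports one.

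The open choices also matter because of who makes them. Data management {19} gives the analysis to the PhD candidate. Implementation {16c} discloses allocation to the same person once the PEMF sessions are complete, so at least some 3- and 6-month visits come after disclosure.

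**Working it through.** The plan states no figure on this point, so there is none to reproduce. The check reads the sections together and then simulates.

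**1. How much is imputed.** Expected dropout is 0.20 × 40 = 8 participants, which leaves 32 complete. Leaving imputation out would not solve the problem: a classical repeated-measures ANOVA drops anyone with a missed visit, and analysing about 32 of 40 would conflict with the intention-to-treat statement in {20c}.

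**2. What Rubin's rules need.** For m imputed sets with estimates Q_k and standard errors SE_k:
- pooled estimate = mean of Q_k
- within-imputation variance W = mean of SE_k²
- between-imputation variance B = variance of Q_k
- total variance T = W + (1 + 1/m)B; with m = 5, T = W + 1.2B

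Analysing one set, or the averaged data, leaves out the B term.

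**3. What the named tests deliver.** The group-by-visit F over two arms and five visits has (2 − 1)(5 − 1) = 4 numerator degrees of freedom, so it is an omnibus statistic and not one difference. U compares ranks. Both can be pooled, but by other means:
- F by a D2-type rule, which combines the m test statistics and penalises their spread.
- Mann–Whitney through the probability index P(Y₁ > Y₀) + ½P(Y₁ = Y₀) and its standard error, to which Rubin's rules then apply.

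Neither pooled result is in VISA-A points.

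**4. Simulation settings.** From the protocol: 20 per arm, five visits, SD 20.25, about 20% dropout, 16-point effect. Assumed: normal scores, monotone dropout, arm in the imputation model, and Mann–Whitney and the mean difference taken at 6 months as an illustration. Correlation was varied: 0.8 or 0.9 per 4 weeks, exchangeable 0.5, and the 0.03 given in {14}. Most runs used m = 5. One set used m = 20, with dropout depending on the last observed score and an effect profile of 0, 8, 16, 16, 16 points. Runs had 500 to 3,000 trials per setting where the count is known.

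**5. Rejection rate with no treatment effect (nominal 5%), range over the runs.**

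| Procedure | Rejection rate |
|---|---|
| One imputed set treated as complete | 8–12% |
| Imputations averaged, one test | 9–12% |
| Any of five sets with p < 0.05 | 17–23% |
| F pooled by D2 | 2.8–4.6% |
| Mann–Whitney index, pooled | 4.8–5.4% |
| Mean difference, Rubin-pooled | 2.8–4.7% |

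Monte Carlo error is small next to these gaps. For a 10% rate over 1,500 trials it is √(0.10 × 0.90 / 1500) = 0.8 percentage points.

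**6. Disagreement between imputed sets about p < 0.05, with a 16-point effect.**
- m = 5: 18–33% of trials for F and 34–40% for Mann–Whitney; a further set of runs gave 23–41% overall.
- m = 20: 46–53% for F and 52–57% for Mann–Whitney. More sets give more chances to straddle 0.05.
- At m = 20 and correlation 0.03, the median smallest and largest p within a trial were 0.012 and 0.246 for F, and 0.004 and 0.194 for Mann–Whitney.

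**7. Power for 16 points when pooled properly (m = 20, correlation 0.03 or 0.5).** D2-pooled F 0.34–0.61; pooled Mann–Whitney 0.53–0.58; Rubin-pooled baseline-adjusted mean difference 0.51–0.63. Moving to the mean difference therefore does not cost power overall compared with the named tests.

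**The case against.** The strongest reply is that the plan can be carried out validly as it stands. A repeated-measures ANOVA is a linear model whose contrasts have estimates and standard errors, F and U can both be pooled, and pooling kept type I error at or below about 5% in the simulations. The article nowhere says that imputations will be averaged, that one set will be chosen, or that unpooled p-values will be reported. The number of imputations and the pooling rule are details that an article commonly leaves to the SAP, which is not shown. Nothing in {20a} forbids reporting a mean difference.

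All of this stands, and it limits the point. A reader might infer that these tests cannot be pooled at all, that the trial must end with conflicting p-values, that it cannot judge an effect against 16 points, or that its type I error will be about 20%. The documents support none of these. The 17–23% figure belongs to a rule (any of five sets counts) that nobody planned.

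It is also true that having two tests over five visits, with neither a deciding test nor a deciding visit, would be ambiguous with complete data. That part is not caused by imputation. A mixed model with arm-by-visit terms gives a difference at each of four follow-up visits, so it does not settle the result either unless a primary visit is named.

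What remains is more than an omitted formula. The protocol chooses three methods that fit together badly for its primary outcome, and even correctly pooled F and U tests give no difference in points.

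**Conclusion.** The point holds as a mismatch of stated methods, not as proof of an invalid analysis. Multiple imputation is planned under missing at random, the primary score goes to two tests whose direct output Rubin's rules cannot combine without a special method, and no between-arm difference is set up for comparison with 16 points.

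If the pooling step is skipped, type I error is about 9–12% instead of 5%, and five imputed sets disagree on significance in roughly a quarter to 40% of trials with a true 16-point effect (lowest single figure 18%, for F). If it is done properly, type I error is held. These sizes rest on normal scores, monotone dropout at the protocol's 20%, and assumed correlations; the Mann–Whitney and averaging results changed little over correlations from 0.03 to 0.9 per 4 weeks. This should be changed, because the change is cheap and gives the trial one interpretable primary result.

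**What to change.** For VISA-A, replace the ANOVA, Mann–Whitney and imputation combination in {20a} and {20c} with:

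1. One likelihood-based mixed model for repeated measures with arm, visit and arm-by-visit terms, an unstructured covariance, and a small-sample degrees-of-freedom correction. It uses every observed visit under the same missing-at-random assumption, without imputation. It also does not assume equal correlation between visits that are unevenly spaced.
2. One primary visit, named before anyone involved in the analysis learns the allocation.
3. The between-arm mean difference at that visit with a 95% confidence interval, read against 16 points.

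If imputation is kept, estimate a baseline-adjusted mean difference at the primary visit in each imputed set and pool it by Rubin's rules. The F and U statistics should not be the pooled quantity.

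Cost: a few sentences, no new data, and SPSS can fit the model. The downside is 5 × 6 / 2 = 15 covariance parameters to estimate from 40 participants, about 32 of them complete, against 2 under compound symmetry; this is why the small-sample correction is needed. The mixed model itself was not simulated here. The figures above support the Rubin-pooled difference directly, and the mixed model rests on standard likelihood theory under missing at random.

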### Plans to give access to the full protocol, participant-level data, and statistical code {31c}

The protocol has been shown on ClinicalTrials.gov (ID: NCT05316961). The participant-level data and statistical code can be provided upon request.

## Oversight and monitoring

### Composition of the coordinating centre and trial steering committee {5d}

The principal investigator will monitor the progress of the study. The trial steering committee are research team members who will participate in participant recruitment, data collection, and management.

### Composition of the data monitoring committee, its role, and reporting structure {21a}

The trial steering committee consists of orthopaedic surgeons, a physiotherapist, and a biostatistician. The orthopaedic surgeons and physiotherapists will participate in data collection and analysis. The biostatistician will monitor data collection and perform interim analysis. There is no independent data monitoring committee as this is not required by the ethics committee. This is a low-risk study as PEMF was implemented as a conventional conservative treatment for patients with other musculoskeletal disorders.

